**Whole-body exercises: 10 movements^c^**																									
	EXE time (min)	25		25		30		30		40		40		45		45		55		55		60		60	
	Sets (rest, seconds)	3 (30)		3(30)		3(30)		3(30)		3(30)		3(30)		3(30)		3(30)		3(30)		3(30)		3(30)		3(30)	
	Work (rest), seconds	30 (15)		30 (15)		40 (20)		40 (20)		50 (25)		50 (25)		60 (30)		60 (30)		70 (35)		70 (35)		80 (40)		80 (40)	
RPE^d^			13-15		14-16		13-15		14-16		13-15		14-16		13-15		14-16		13-15		14-16		13-15		14-16
Calories/session			250-370		320-400		390-400		400-500		450-560		500-580		580-660		600-680		620-700		250-370		320-400		390-400
Total calories/week			750-1100		950-1200		1170-1200		1200-1500		1800-2000		2000-2200		2300-2600		2400-2700		3000-3200		3200-3500		3700-3900		3800-4000

^a^EXO: aerobic exercise.

^b^MHR: maximum heart rate.

^c^In the whole-body section, 10 movements are performed in 3 sets, which increases based on the addition of long-term load and training volume, including a change in resting interval intensity (active recovery and low intensity/recovery such as jogging). Based on the timing of the table, in the range between each set, there is a constant passive recovery period of 30 seconds.

^d^RPE: rate of perceived exertion; calculated as the maximal effort movement for each subject in 30 seconds based on a minimum of 6 when at rest and 20 at the maximum heart rate. During the initial session, we determined the RPE to range from 13 to 15.

### Training Exercise or Multimodal Program for One Session

In both groups, participants report their weekly exercise with an exercise physiologist to estimate caloric intake and ensure compliance. After 1 minute of rest after completing the aerobic exercises, whole-body exercises are performed, consisting of 10 repetitions of the movement, in such a way as to replace the energy expenditure specified in the program and prevent repetition of the exercises. The body weight training pattern shows the energy expenditure during exercise, and the calories burned for the warm-up and cool-down periods are also calculated from the smartwatch and verified from the ACSM formula [39]. To avoid fatigue and repetition of movements during the training period, the movements are changed in a variety of ways every week, as shown in Figure 2.

**Figure 2 figure2:**
[figure not shown]
Specific exercises and drills applied in the program. In the aerobic part, participants can choose from the exercises of the first row. In the whole-body section, participants can choose 2 movements from the exercises of the 2nd row and 4 movements from the exercises of the 5th row to prevent the repetition of exercises in each session.

## Results

Preliminary results show that the high-calorie-expenditure training program more than doubled weight loss and reduced fat mass, along with a further decrease in waist circumference. Figure 3 shows the changes in the body composition of the three groups. The overall goal of increasing exercise energy consumption was achieved, with an increase in energy consumption in physical activity of more than 3500 calories per week in the high-calorie-expenditure group and up to 1200 calories per week in the standard-calorie-expenditure group. Preliminary statistical analyses indicate significant differences between the stages and in the interaction of time and group. Additional analyses of functional parameters, lipid profiles, inflammatory factors, and blood indicators are ongoing.

**Figure 3 figure3:**
[figure not shown]
Changes in BMI, weight, fat content, and muscle in the the three groups. CG: control group (no exercise); HC: high-calorie-expenditure group; SC: standard-calorie-expenditure group.

## Discussion

### Principal Findings

The primary results of this study show that high-calorie-expenditure exercise is superior to regular exercise in terms of achieving weight loss in women with overweight. Our results demonstrate that both types of exercise (high and standard calorie expenditure) led to significant weight loss (*P*=.003). Significant changes were also observed in muscle percentage (*P*=.05) and BMI (*P*=.05) of the high-calorie-expenditure group after 12 weeks. The functional tests also showed that both exercise programs had a positive effect on the participants.

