**Objective:**

The aims of this research protocol are to (1) develop a high-calorie-expenditure training program to cover target calorie expenditure according to the trainability of women classified as overweight (according to a BMI of 25-29.9 kg/m^2^); (2) determine the effect of high-calorie-expenditure workouts on conditioning, glycemic variables, and body composition; and (3) evaluate the implementation of the intervention and results in comparison with outcomes obtained under a standard-calorie-expenditure training program.

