**Results:**

Preliminary results show significant weight loss in both the high- and standard-calorie-expenditure groups (*P*=.003). Significant improvements were also found in muscle percentage (*P*=.05) and BMI (*P*=.05) for the high-calorie-expenditure group. Analyses are ongoing for glycemic indices, inflammation factors, and blood parameters.

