### Sample Size and Group Allocation

The sample size was determined by a power calculation to detect group differences in the primary outcomes. Previous randomized controlled trials of exercise interventions have demonstrated effect sizes between 0.24 and 1.17 in similar populations for cognitive performance measures following aerobic interventions. To obtain 80% statistical power with an α level of .05, using an *F*-test for three independent groups and an effect size of 0.6, the sample size required was determined to be 30 participants using G*Power version 3.1. Among 60 applicants, a total of 33 participants have been recruited after primary evaluations, including height, weight, fat percentage, waist circumference, BMI, confirmation of the activities performed in the last year, and the lack of medical restriction to participate in the exercise training.

Following written informed consent of all participants and an explanation of the risks and benefits of the research, participants were randomized into the three groups: high-calorie-expenditure (n=11), standard-calorie-expenditure (n=11), and control (n=11) groups.

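### The claim that high-expenditure exercise beats standard exercise for weight loss has no high-versus-standard result behind it in the visible text, and the 80% power covers only the three-group omnibus test

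*Protocol article*

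**What the plan says.** The third aim in the Abstract (Objective) is to evaluate the intervention "in comparison with outcomes obtained under a standard-calorie-expenditure training program". The Abstract (Methods) also sets a comparison with the no-exercise control.

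The section Sample Size and Group Allocation names its test only for the size calculation: "To obtain 80% statistical power with an α level of .05", an F-test "for three independent groups and an effect size of 0.6", and "the sample size required was determined to be 30 participants using G*Power version 3.1". The trial then randomized 33 women, 11 to each arm. No pairwise contrast is named there.

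The preliminary findings are as follows:
- Abstract, Results: "significant weight loss in both the high- and standard-calorie-expenditure groups", with one P value of .003. Muscle percentage and BMI in the high-expenditure group have P=.05 each.
- Results section: weight loss more than doubled under the high-expenditure program, and the analyses show "significant differences between the stages and in the interaction of time and group". No outcome, statistic or pairwise follow-up is attached to that statement.
- Discussion, Principal Findings: "high-calorie-expenditure exercise is superior to regular exercise in terms of achieving weight loss in women with overweight". The Abstract's Conclusions section makes a similar claim.

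**The concern.** The conclusion compares two exercise programs. The figures printed with it answer other questions: whether women in both exercise arms lost weight, whether the high-expenditure arm changed on two other measures, and whether three arms, one of them without exercise, followed the same course over time. Any of these can be significant when the two exercise programs work equally well.

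The 80% power also belongs to the three-arm question. A reader who carries it over to high versus standard would overrate what 11 women per arm can show about that contrast, unless the true means happen to lie in a favourable pattern. At stake is the article's main efficacy conclusion, and with it the case for asking women to train five times a week rather than three.

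**Working it through.** **1. Inputs.** From Sample Size and Group Allocation: three groups, α=.05, 80% power, effect size 0.6, N=30 required, 11 per arm randomized. The article does not name the effect-size metric; 0.6 is read here as Cohen's f. It gives no spacing of the means and no SD. A two-sided test and no dropout are assumed.

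**2. Reproducing the stated size.** In a one-way ANOVA the F statistic has noncentrality λ = N·f².
- N=30: λ = 30 × 0.36 = 10.8 on 2 and 27 df, power 0.800. The stated 30 is reproduced, which supports reading 0.6 as f.
- N=33: λ = 33 × 0.36 = 11.88 on 2 and 30 df, power 0.843.

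**3. What f=0.6 implies for high versus standard.** By definition f² = Σ(μᵢ − μ̄)²/(3σ²). Different patterns of means share the same f. Let d be the high-minus-standard difference in SD units. Power is from a two-sided t-test with pooled error (30 df), 11 per arm, and noncentrality d·√(11/2).

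| Pattern with f = 0.6 | d | Power |
|---|---|---|
| High equals standard, only control differs | 0 | 5% (the α level) |
| Equally spaced, standard midway | 0.6 × √1.5 = 0.735 | 38.5% |
| Only high differs from the other two | 0.6 × 3/√2 = 1.273 | 82% |
| High and standard are the extremes, control midway | 2 × 0.735 = 1.470 | 92% |

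Using only the two arms for the error term (20 df), the equally spaced case gives 37.5%. At d=0.735, 80% power with that two-arm test needs 31 per arm.

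**4. Can the omnibus result stand in for the contrast?** In the first row of the table the true high-standard difference is zero, yet f is still 0.6 and the omnibus test at N=33 still has 84% power. A significant three-arm result, including a three-arm time-by-group interaction, therefore does not establish that high beats standard.

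**5. What baseline adjustment would add.** A time-by-group analysis already uses each woman's baseline. With equal variances at both times and baseline-to-week-12 correlation r (assumed), ANCOVA has (1+r)/2 of the change-score variance: 0.85 at r=.7 and 0.90 at r=.8, a cut of 15% or 10%. If 0.735 is on the change scale, d becomes 0.735/√0.85 = 0.797 or 0.735/√0.90 = 0.775. On 29 df, power then rises from 38.5% to about 44% or 42%.

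**The case against.** The strongest reply is that the article is a protocol with preliminary results. It may leave its analysis model to a fuller document, Figure 3 may carry pairwise tests, and comparison with control is a stated aim that an omnibus test does serve. All of that stands. It cannot be said that high versus standard was never tested, nor that an F-test is the planned analysis; the F-test appears only in the sizing. What remains is that the article asserts the conclusion in its text and gives no high-versus-standard result there.

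A second reply is that 38% is not a property of this trial. That also stands. It depends on standard lying midway between control and high, and the favourable patterns reach 82% and 92%. The range shows that the sizing does not secure power for this contrast; it does not show that power is low.

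Three stronger readings are tempting and should not be drawn:
- A reader might infer that P=.003 for weight and P=.05 for BMI contradict each other, since height is fixed. The article attaches the first to both exercise arms and the second to the high arm alone. If .003 came from a pooled paired test of 22 women (an assumption), t = 3.35 on 21 df. The same standardized change in 11 women gives t = 3.35/√2 = 2.37 on 10 df, P=.039, not far from .05. No conflict is shown.
- A reader might infer that baseline values go unused. The time-by-group analysis uses them.
- A reader might want high versus standard declared the single primary contrast now. With preliminary weight results known, that would be a choice informed by the data.

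**Conclusion.** The concern holds in this form. The superiority statement is not supported by any high-versus-standard result in the visible text, and neither the P values given nor the three-arm interaction can replace one. The 80% power at N=30 is correctly computed for the omnibus test (0.843 at N=33) and does not extend to the contrast in the conclusion. Power for that contrast is about 38% under equally spaced means, with a range of 5% to 92% over patterns compatible with the same effect size. These figures assume that 0.6 is Cohen's f, two-sided α=.05 without multiplicity adjustment, and no dropout. It should be corrected because it concerns the article's main efficacy conclusion.

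**What to change.** 1. Report the high-minus-standard difference in weight change with a 95% CI. An ANCOVA of the week-12 weight on arm, adjusted for baseline weight, is preferable, though its gain over change scores is modest. Give each exercise arm against control alongside.
2. Withdraw or soften the superiority wording in Principal Findings, and the matching sentence in the Abstract's Conclusions, unless that interval supports it.
3. In Sample Size and Group Allocation, state that the 80% applies to the omnibus test only. Add the power for high versus standard with the assumed spacing of means and the range.
4. Do not describe high versus standard as a prespecified single primary contrast unless a document that predates the results fixed it. Otherwise say that the contrast was emphasized after preliminary weight results were known.

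Cost: a rerun on data already collected, a few changed sentences, and a less favourable power statement. No new measurements are needed.

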### Comparison With Prior Studies

In the case of severe and acute illnesses such as COVID-19, the effects of the disease not only decrease physical activity but also cause obesity problems in women [40]. Consequently, living an active lifestyle and monitoring one’s diet by counting daily calories can be a helpful approach to lose weight. The preliminary results of this study show that the average calorie expenditure of group-based mixed high-calorie-expenditure exercise (including the warm-up and cool-down periods) was 800 kilocalories, as estimated by the Apple Watch calorimeter. By contrast, the energy consumption per session for the standard-calorie-expenditure group was only 450 kilocalories. Results from a limited number of studies measuring energy expenditure with caloric intake have been mixed. Overall, participants performing high- and standard-calorie-expenditure exercises burned 3700 and 1350 calories, respectively. Brisebois [41] showed that 30 adults (19-60 years old, 50% women) had an average energy expenditure of 7.5 kilocalories/minute in a 60-minute CrossFit session. In a 2018 study [42], a 10-month implementation of an integrated neuromuscular circuit-type training program in small groups resulted in (1) an increase in daily energy expenditure relative to energy intake, leading to a decrease in body mass and fat; (2) an increase in strength and cardiovascular performance; and (3) a high adherence rate. Exercise-induced gains were reduced but not lost after a 5-month no-exercise period. The exercise program involved noninjury HIIT using resistance exercises of the whole body and cardiovascular activities with a limited time commitment and organized in a small group, resulting in favorable adaptation in the body and fat mass of people with overweight and obesity. Circuit-type neuromuscular exercise training protocols using only body-weight exercises could reduce body mass and fat and improve strength and endurance performance in women. These changes were attributed to an increased resting metabolic rate and lean mass, leading to increased energy expenditure. Weight/fat recovery from nonexercise was limited, suggesting that this type of exercise training may promote the long-term maintenance of weight loss in adults with overweight [42]. Willis et al [43] recorded the energy expenditure of 20 men and women during a 40-minute training session delivered by video. The findings indicated that the participants burned an average of 392 kilocalories per session (9.8 kilocalories per minute). Differences in the type and intensity of exercise throughout the session can explain the differences in the results of our study and those of previous studies. In addition, Willis et al [43] found a significant difference in energy expenditure between men and women of ~134 kilocalories per session (3 kilocalories/minute). This previous study compared the traditional exercise method with other methods. Therefore, it was not based on whole-body training and the sessions all involved steady-state exercise at the same intensity. Weight training is usually performed at high intensity for short periods with longer periods in between, which is expected. In this study, the timing of the training protocols was modified, but the protocol was similar to that of resistance training.

Monteiro et al [44] indicated that CT requires the consumption of more calories than resistance training. CT, resistance training, and combined exercises such as using a treadmill or bicycle have not been compared. Skelly et al [45] compared single sessions of two cycling protocols, HIIT and moderate steady-state endurance exercises, with a constant caloric-expenditure protocol, showing that oxygen consumption was higher in the steady-state protocol than in the HIIT protocol. However, the steady-state protocol was of a much longer duration (50 vs 20 minutes). Therefore, it can be assumed that if the duration of the two sessions were equal, the HIIT protocol would burn more calories [45]. A 6-month pilot study conducted at Pennington Biomedical Research Center [46] compared 25% CR achieved through (1) dietary restriction alone and (2) a combination of dietary restriction and exercise. Compared to the free control group, CR and exercise led to an increase in energy expenditure by 12.5%. The primary hypothesis was that CR would attenuate primary aging processes, as represented by the presence of metabolic adaptation, which is a reduction in the rate of energy expenditure beyond what would be expected on the basis of body size. In support of the hypothesis, they found that the mass-adjusted sleeping energy expenditure was reduced after 6 months of CR and CR+exercise, indicating metabolic adaptation and perhaps a delay of primary aging [46].

Among the multifaceted combined exercises highlighted above, body weight and aerobics exercises are highly valuable and can provide powerful results for middle-aged individuals. In particular, these exercises have been shown to improve cardiovascular performance and respiratory health, reduce weight, reduce body fat and increase muscle mass, improve blood circulation, improve bone and skeleton conditions, and finally improve the quality of life of middle-aged people [47,48]. In addition, in line with the prominent health-related effects of a multimodal exercise program, Batrakoulis et al [49] showed that combined aerobic and resistance exercise was the most effective method and hybrid exercise was the second most effective method for cardiometabolic health outcomes in adults with overweight and obesity, indicating higher efficacy for multicomponent exercise interventions compared to single-component methods such as continuous endurance training as a periodic exercise. Subgroup analysis of resistance training further showed that the effects of different types of training were mediated by gender [49]. This study also supports recent findings and exercise guidelines for individuals with overweight/obesity, highlighting the importance of a multicomponent exercise approach to improving cardiometabolic health. Accordingly, physicians and health care professionals should prescribe multicomponent exercise interventions for adults with overweight and obesity to maximize clinical outcomes [48]. In the present protocol, ACSM guidelines were suggested with some changes to increase the caloric expenditure of the exercise. Although HIIT exercises can also be effective, according to international guidelines for physical activity and exercise and guidelines for sedentary behavior, obesity, and type 2 diabetes, it is suggested that before starting HIIT exercise protocols, individuals should achieve a baseline level of physical fitness. Participating in a preliminary training program before using HIIT can help to reduce the risk of musculoskeletal injury while ensuring a positive training experience from the outset [50]. A gender difference in outcomes is anticipated because of variabilities in body weight and the higher rate of weight loss in men than in women.

### Limitations

This study has several limitations. The physical activity levels of the participants obtained with the IPAQ were not installed in the software and mobile phones of each participant. However, the results were determined to be satisfactory after answering the questionnaire. In addition, because this investigation started immediately after the lifting of restrictions related to the COVID-19 pandemic to conform with health protocols, it is possible that this long period of isolation had mental and psychological consequences on the participants.

When developing a target exercise interval, it is important to consider relevant variables to ensure that energy expenditure is at the level necessary for the health of all people. Further research is needed to confirm our results and determine the optimal group-based workouts that maximize caloric burn while increasing adaptation. In this study, we have confirmed the applicability of 5 high-calorie-expenditure training sessions in women over 35 years old, with benefits of weight loss, fat mass reduction, and muscle mass increase. In addition, our initial analyses suggest benefits with respect to inflammation and the lipid profile. However, the effects of these exercises on the immune system, bone conditions, reproduction, and other health facets remain unclear. It will also be valuable to examine the effect of this type of exercise over the longer term for 6 months to 1 year.

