Designing an exercise program above the standard level of calorie expenditure, especially for sedentary people, can be challenging. High-caloric exercises could act as a double-edged sword; on the one hand, a reduction of adipose tissue brings benefits of reducing metabolic syndrome, while on the other hand, high-intensity activity can be accompanied by increased inflammation. The restriction of energy intake below the amount necessary to maintain weight, known as caloric restriction (CR), can extend the lifespan even for people with normal weight. CR significantly extended lifespan in various preclinical studies with animal models; moreover, CR of approximately 30% was shown to increase life expectancy in humans by 1-5 years [13]. Thus, individuals with higher metabolic rates tend to have shorter lifetimes [14].

The development of this hypothesis stems from the inverse association observed between the rate of metabolism of mammals (by body weight and per day) and lifespan [15]. Mechanistically, the rate of life theory is supported by the free radical theory of aging [16], which postulates that 1%-3% of the oxygen consumed in mitochondrial ATP production produces reactive oxygen species (ie, oxidative stress) [17]. Therefore, with more energy expended as a function of time (ie, with aging) or because of a high metabolic rate, there is a greater likelihood of oxidative damage to the cells and tissues [18]. Oxidative stress also disrupts many molecular and cellular structures and functions. Low physical activity exacerbates this mechanism by reducing mitochondrial function and oxidation capacity in cells and tissues. Physically, caloric excess and low physical activity increase the fat mass and cause declines in skeletal muscle mass, strength, and physical fitness [19]. During a 6-month pilot study at Pennington Biomedical, participants in both CR groups lost 10% of their body weight [20] with a 25% reduction in total fat mass and a 27% reduction in visceral fat [11], the fat deposit type most closely linked to the development of metabolic diseases [16].

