## Methods

### Study Design

This study was designed to assess the effect of a 12-week multimodal exercise program intervention under two different calorie-expenditure conditions (high=3000 calories/week vs standard=1200 calories/week) and a no-exercise waitlist control group. The study was conducted at the University of Tabriz in the southeastern region of Azerbaijan, Iran. This study was registered in the Iranian Registry of Clinical Trials (IRCT20220202053916N1).

Figure 1 summarizes the proposed 12-week training plan. Participants will be allocated to three groups: a high-calorie-expenditure group, standard-calorie-expenditure group, and control group. In the high-calorie-expenditure group, participants will engage in 3 sessions of exercise per week for 45 minutes with an estimated expenditure of 650-900 calories per week for weeks 1 and 2. In the third week, they will also have 3 sessions per week with a training duration of 50 minutes per session at an estimated calorie expenditure of 750-1200 per week. In the fourth week, the duration of the exercise will be increased to 60 minutes with 3 sessions per week, thereby increasing the calorie expenditure of the exercise by approximately 1200-1300 per week. In the fifth and sixth weeks, the training time will increase to 70 minutes and the number of training sessions will also increase to 4 sessions per week, resulting in calorie expenditure of approximately 1800-1500 and 1600-2000 calories per week, respectively. In week 7, the training duration will increase to 4 sessions of 80 minutes each with estimated weekly calorie expenditure of 1800-2200. In weeks 8 and 9, the training duration will increase to 90 minutes with expenditure of 1900-2500 calories/week. In the last 3 weeks, the number of sessions will reach 5 with weekly sessions of 95, 100, 110, 110, and 110 minutes, respectively accounting for 2700-3100, 3000-3500, and 3300-3700 calories consumed in week 10, 11, and 12, respectively.

The standard-calorie-expenditure group will receive a 12-week exercise program in the form of 3 training sessions. In weeks 1 to 4, each session will comprise 40 minutes of exercise with 650-900 calories consumed per week; in weeks 5 to 8, sessions will last 60 minutes with 1000-1200 calories consumed per week; and weeks 9 to 12 will involve an increase in the training time to 80 minutes with expenditure of 1200-1500 calories per week.

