### High-Calorie-Expenditure Training Protocol

Compared to the standard program, the exercise prescription for the high-calorie-expenditure group has a longer duration (45-110 vs 40-65 minutes per session), lower intensity (50%-75% vs 60%-85% VO_2_ max), and more frequent exercise (5 vs 3 times a week). Walking and running are the preferred forms of exercise to maximize calorie burning in comparison to weight training (cycling or rowing), which burns fewer calories. In the high-calorie-expenditure group, the goal of exercise expenditure is 3000-3500 kilocalories per week [30], which is achieved after 2-4 weeks of gradual lengthening of the exercise periods. The training protocol also lasts for 12 weeks, with 45 minutes of whole-body training at 65%-85% VO_2_ max consuming 1200 kilocalories per week; based on the principle of gradual overload with increasing weight, the energy expenditure at the end of the training period will be 3500 kilocalories. The calories increase per week [37] and the training time increases to 112 minutes. The main element of training is the same as that of the standard protocol, which starts with 3 sessions per week and gradually increases to 5 sessions per week, although the duration of each training session will be twice that for the standard-calorie-expenditure program in each step (Table 3).

In addition, the participants will be taught how to measure their heart rate in 10 seconds using the two index and middle fingers to find the pulse of the carotid artery of the neck and the pulse of the wrist. Participants will report their heart rate during aerobic exercise when requested by the investigator [38]. After 1 minute of active rest, each participant will begin a full-body exercise.

**Table 3 table3:** High-calorie-expenditure training protocol on a weekly and session basis (3 sessions/week).

Parameter			Week 1		Week 2		Week 3		Week 4		Week 5		Week 6		Week 7		Week 8		Week 9		Week 10		Week 11		Week 12
Total time (min)			135		135		150		150		246		280		340		340		475		525		530		530
EXE^a^ (min)			20		20		20		30		30		30		40		40		40		50		50		50
MHR^b^, %			65-75		70-85		65-75		70-85		65-75		70-85		65-75		70-85		65-75		70-85		65-75		70-85

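### The article declares five high-expenditure sessions a week confirmed as applicable, on preliminary group-level data from an arm of 11 women planned to train at that frequency only in the last three or four weeks

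*Protocol article*

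**What the plan says.** All references are to the protocol article.

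- **The conclusion.** Limitations: "we have confirmed the applicability of 5 high-calorie-expenditure training sessions in women over 35 years old". The sentence just before it says that more research is needed to confirm the results.
- **The question behind it.** The end of the Introduction asks whether these women have the capacity for 12 weeks of high-expenditure training, so this is a stated aim and not a side remark.
- **Arm size.** Sample Size and Group Allocation: "high-calorie-expenditure (n=11), standard-calorie-expenditure (n=11), and control (n=11) groups".
- **Frequency in the text.** Study Design gives three sessions a week in weeks 1 to 4. From week 5, "the number of training sessions will also increase to 4 sessions per week". Then, "In the last 3 weeks, the number of sessions will reach 5".
- **Frequency in the table.** The caption of Table 3 reads "High-calorie-expenditure training protocol on a weekly and session basis (3 sessions/week", but its weekly minutes rise well beyond three sessions.
- **Exclusions.** Study Population lists onset of menopause during training, disruption of the cycle, and missing more than 30% of sessions.
- **Delivery data.** Results gives more than 3500 calories a week in the high arm. Comparison With Prior Studies gives about 800 kilocalories per session and 3700 calories overall.
- **Inflammation and lipids.** Limitations: "our initial analyses suggest benefits with respect to inflammation and the lipid profile". Results: "Additional analyses of functional parameters, lipid profiles, inflammatory factors, and blood indicators are ongoing". The Abstract also calls the inflammation analyses ongoing.

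**The concern.** A study question is reported as settled while the results are still called preliminary and the data that would settle it are not shown. To judge whether women can train five times a week, a reader needs to know how many of the 11 did so, for how long, and what became of the others. The article gives no attendance, withdrawal or exclusion counts, and no EAT-26 or menstrual results.

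The exclusion rule makes this worse. Cycle disruption and poor attendance are two ways in which a woman could show that the program does not suit her, and both are grounds for exclusion. If excluded women are left out of the reported averages, the conclusion is partly circular: the program proves applicable in those to whom it could be applied.

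The inflammation and lipid sentence has a similar weakness. A benefit is suggested without a figure, for analyses that the same article says are unfinished.

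**Working it through.** **1. The plan's own sample size.** Inputs: one-way F-test, three groups, effect size 0.6 (taken as Cohen's f), alpha .05, power 80%, stated total 30. With noncentrality N × f²:

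- N = 30: 30 × 0.36 = 10.8, df 2 and 27, power 0.800. The stated 30 reproduces.
- N = 33: 33 × 0.36 = 11.88, df 2 and 30, power 0.843.

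This calculation supports a comparison between groups. It does not size a statement about feasibility in one arm of 11.

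**2. Weeks planned at five sessions.**

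- Study Design: weeks 10 to 12, so 3 of 12 weeks (25%).
- Table 3, weekly minutes divided by aerobic plus whole-body minutes per session: week 8, 340/85 = 4.0; week 9, 475/95 = 5.0; week 10, 525/105 = 5.0; weeks 11 and 12, 530/110 = 4.8. That is about five sessions in weeks 9 to 12, so 4 of 12 weeks (33%).
- Table 3 calories cannot settle the difference. The per-session ranges for weeks 10 to 12 repeat those of weeks 1 to 3. Set against the weekly totals they would need about 9 to 13 sessions (week 10: 3200/250 = 12.8 and 3500/370 = 9.5).

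The text, the table minutes and the caption disagree and must be reconciled.

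**3. Other measures of exposure.** Assuming four sessions a week continue in weeks 8 and 9 (Study Design states no change), the text gives 4×3 + 5×4 + 3×5 = 47 sessions, of which 15 (32%) fall in five-session weeks. By Table 3 minutes, weeks 10 to 12 are 1585/3836 = 41% of training time and weeks 9 to 12 are 2060/3836 = 54%.

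**4. What the 30% rule guarantees.** A woman who attends three of five sessions in each of weeks 10 to 12 misses 6/47 = 12.8%. She never trains five times a week, yet she stays within the rule. Remaining in the study is therefore no evidence of having trained at that frequency.

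**5. What 11 women can show at best.** The article gives no counts, so the following is a best-case assumption.

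- All 11 complete: exact two-sided 95% lower limit = 0.025^(1/11) = 0.715, about 72%.
- Equivalently, with no events in 11, the upper limit is 1 − 0.025^(1/11) = 28.5% two-sided, or 1 − 0.05^(1/11) = 23.8% one-sided.
- The chance that none of 11 women shows an event with a true rate of 10% is 0.9^11 = 31%.

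**The case against.** The best defence is that the sentence claims applicability, not safety or tolerability, and that delivery data exist. The energy goal is reported as met, with more than 3500 calories a week. If the 3700 calories and the 800 kilocalories per session refer to the same week, which the article does not say, 3700/800 = 4.6 sessions, roughly what was planned. The week-by-week progression is also printed, so an attentive reader will not assume 12 weeks at five sessions. The results are called preliminary several times, and the same paragraph says that effects on reproduction and other areas remain unclear. Outcome tables can be left to a results paper.

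Much of this stands. These stronger readings should not be drawn:

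- **That the article declares the program tolerable or safe.** It does not use those terms.
- **That missing injury, EAT-26 or menstrual tables are a fault of the protocol.** They can come later, and the article does not describe an injury record from which counts could be taken.
- **That an inflammation benefit was asserted before any analysis.** An initial look can coexist with unfinished analyses.
- **That inflammation is a designated harm outcome.** The Introduction says "high-intensity activity can be accompanied by increased inflammation", but it ties this to intensity, and the high arm is described as the lower-intensity program.

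The defence does not rescue the word confirmed. The energy figures are averages with no attendance or denominator. The hedges attach to other statements, and the one immediately before it contradicts it.

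**Conclusion.** The point holds as one about a printed conclusion that outruns the design and the data shown. Five sessions a week were planned for three weeks (text) or about four (Table 3 minutes), in an arm of 11. The article does not show how many women trained at that frequency. Even perfect completion would leave the true completion rate possibly as low as about 72%.

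Two assumptions matter. The 72% is hypothetical because no counts are given. That the energy averages cover only women who were not excluded is a possibility left open by the exclusion rule, not something the article states.

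A reader might infer that the program failed or did harm. Nothing in the article supports that: applicability is not shown either way.

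**What to change.** - **Limitations, the sentence on applicability.** Replace it with a preliminary statement: a 12-week program progressing to five sessions a week in its final weeks was tested in 11 women.
- **Frequency.** Reconcile Study Design, the Table 3 minutes and the Table 3 caption on when five sessions a week apply.
- **Any later conclusion on applicability.** Base it on all 11 women randomised to the arm. Count withdrawals and the exclusions listed in Study Population as non-completion, report attendance in the five-session weeks, and give the completion proportion with an exact 95% interval. Report the EAT-26 results, already planned at three stages, beside it.
- **Inflammation and lipids.** Remove the suggested benefit, or state that no supporting data are shown, until the analyses that the Abstract and Results call ongoing are finished.

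The immediate cost is rewording and a less favourable conclusion. The later report needs attendance and reasons for leaving for all 11 women. Design, sample size and clinical management are untouched.
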